### Participants

All patients admitted to ICUs will be screened and evaluated on the day of admission. Patients who meet the inclusion criteria and do not meet the exclusion criteria will be invited to participate in the study.

Inclusion criteria:Over 18 years of age at the time of diagnosisWritten informed consent is signed by the subject or the authorized representativePatient diagnosed with SCAP according to the guidelines for the diagnosis and treatment of community-acquired pneumonia in Chinese adults (2016 Edition), formulated by respiratory branch of Chinese Medical Association. If a patient simultaneously meets the diagnostic criteria of CAP (shown in Table 1) and one of the following major criteria or more than three minor criteria, he/she can be diagnosed as SCAP

**Table 1 Tab1:** Clinical diagnostic criteria of CAP

1. Onset of illness in the community	
2. Clinical manifestations	
• Recent cough, expectoration, or the aggravation of symptoms of original respiratory diseases, with or without purulent sputum, chest pain, dyspnea, and hemoptysis	
• Fever	
• Signs of pulmonary consolidation and/or moist rales were presented	
• Peripheral white blood cell counts > 10×10^9^ / L or < 4×10^9^ / L, with or without left shift of nucleus	
3. New patchy infiltrations, pulmonary consolidations, “ground-glass,” or interstitial changes are shown in chest imaging, with or without pleural effusion.	

Clinical diagnosis of CAP can be established after meeting items 1, 3, and any one of the item 2, and excluding pulmonary tuberculosis, pulmonary tumor, noninfectious pulmonary interstitial disease, pulmonary edema, atelectasis, pulmonary embolism, pulmonary eosinophilic infiltration, and pulmonary vasculitis

Major criteria:Invasive mechanical ventilationSeptic shock with the need for vasopressors

Minor criteria:Respiratory rate ≥30 breaths/minPaO_2_/FiO_2_ ratio≤250 mmHg (1mmHg= 0.133kPa)Multilobar infiltratesConfusion/disorientationBlood urea nitrogen level≥7.14mmol/LHypotension (systolic blood pressure< 90mmHg) requiring aggressive fluid resuscitation

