### Secondary outcomes

Twenty-eight-day mortality (death proportion within 28 days of randomization)Sixty-day mortality (death proportion within 60 days of randomization)Ventilator-free days at 28 days (the number of days free from mechanical ventilator support in the first 28 days following randomization)Mechanical ventilation duration at 28 days (the number of days during mechanical ventilation within 28 days of randomization).Endotracheal intubation rate (the proportion of patients requiring endotracheal intubation within 28 days of randomization)Time for temperature recovery (the number of days required for body temperature to return to normal)Duration of vasopressors use (the number of days required for continuous use of vasopressors)Serum CRP and interleukin-6 level at day 5 following randomizationHospital stayFrequency of nosocomial infections (the number of ventilator-associated pneumonia, blood stream infection or candidemia within 28 days of randomization)Gastrointestinal hemorrhage (the proportion of gastrointestinal bleeding patients requiring additional medication, blood transfusion, or surgical intervention within 28 days of randomization)Hyperglycemia (the proportion of patients with hyperglycemia requiring insulin injection within 28 days of randomization)

All adverse events and other unintended effects of trial interventions or trial conduct will be collected and documented, regardless of severity. Participants who suffer harm from these events will be compensated accordingly.

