### Sample size

On the basis of previous study [12], it is calculated by Tukey-Kramer test that 220 participants will be required (55 in each group) to detect a difference of 50mmHg in the PaO_2_/FiO_2_ ratio between groups, assuming a standard deviation (SD) of 50mmHg in the control group (80% power, *α*= 0.05). If the follow-up rate is assumed to be 90%, 244 participants with 61 in each group will be needed. Sample size calculation was performed by PASS 11 software.

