### Statistical analysis

We will show *n* (%) for categorical variables and median (interquartile range) for continuous variables with non-normal distribution or mean (SD) for those with normal distribution. Data for the primary and secondary outcome will be analyzed on intention-to-treat analysis, and missing data will be handled by multiple imputation method. If variances are equal, comparison of continuous variables will be evaluated by one-way analysis of variance, followed by the least significance difference procedure; otherwise, the Games-Howell procedure will be followed. The *χ*^2^ test followed by the Bonferroni method will be used to evaluate the comparison of categorical variables. Subgroup analysis will be used when appropriate. SPSS 18.0 software will be employed for statistical analysis. Significance level is set at 0.05.

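### The intubation rate is defined over all patients although invasive ventilation alone can qualify a patient for entry; restricting it to patients not intubated at randomisation is a cheap improvement

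*Protocol article*

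**What the plan says.** Under Secondary outcomes, the protocol article defines the "Endotracheal intubation rate (the proportion of patients requiring endotracheal intubation within 28 days of randomization". This fixes a numerator, a denominator and a time window. It does not limit the count to new intubations or to patients who start without a tube.

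Under Participants, a patient with community-acquired pneumonia is classed as severe on meeting "one of the following major criteria or more than three minor criteria, he/she can be diagnosed as SCAP". The list of major criteria reads "Major criteria:Invasive mechanical ventilationSeptic shock with the need for vasopressors". Invasive ventilation alone is therefore one of three routes into the trial. The others are septic shock on vasopressors and a sufficient number of minor criteria. No exclusion criterion removes ventilated patients.

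Under Statistical analysis, "Data for the primary and secondary outcome will be analyzed on intention-to-treat analysis", so the denominator is every randomised patient.

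A second outcome is built in the same way: "Hyperglycemia (the proportion of patients with hyperglycemia requiring insulin injection within 28 days of randomization". The only exclusion that touches on this is for diabetes that is not under control. Patients with controlled diabetes, including any who use insulin, remain eligible.

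**The concern.** An intubation rate is meant to show whether treatment spares patients the tube. A patient who already has one at randomisation has no first intubation left to prevent. Two problems follow if such patients are in the denominator.

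- **Ambiguity.** On one reading the patient needs intubation during the 28 days and is an event from day 0. On the other the patient has no new event. The article does not choose, and the two codings give different rates and different relative risks from the same data.
- **Dilution.** Under either coding, the absolute difference between groups is smaller than the difference among patients who could benefit.

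For hyperglycaemia the stake is on the safety side. The trial sets out to weigh efficacy against complications across doses. Events that come from insulin use before the trial would be added to every group, placebo included.

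**Working it through.** The article gives no expected rate, effect or power for the intubation outcome, so it has no figure to reproduce.

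**Inputs from the article**
- Group size: "244 participants with 61 in each group will be needed", so n = 61 per group.
- "Significance level is set at 0.05". Sidedness is not stated; two-sided is assumed.

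**Assumed inputs (not in the article)**
- f, the share intubated at randomisation, taken as equal in the groups.
- pC and pT, the rates of new intubation among patients at risk in a control and a treated group.
- No re-intubation among patients intubated at entry.

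**Risk difference and relative risk**
- Counted as non-events: rate = (1−f)p. Risk difference = (1−f)(pC−pT). Relative risk = pT/pC, unchanged.
- Counted as events: rate = f+(1−f)p. Risk difference = (1−f)(pC−pT). Relative risk = [f+(1−f)pT]/[f+(1−f)pC], closer to 1 than pT/pC.

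**Example: f = 0.5, pC = 40%, pT = 25%** (at-risk difference 15 points, relative risk 0.25/0.40 = 0.625)
- Events: 0.5+0.5×0.40 = 70% and 0.5+0.5×0.25 = 62.5%. Difference 7.5 points, relative risk 0.625/0.70 = 0.89.
- Non-events: 0.5×0.40 = 20% and 0.5×0.25 = 12.5%. Difference 7.5 points, relative risk 0.125/0.20 = 0.625.

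**Power for one pair of groups:** Φ[(d − 1.96·SE0)/SE1], where d is the risk difference and SE0 and SE1 are its pooled and unpooled standard errors.
- Events, n = 61: (0.075 − 1.96×0.0856)/0.0854 = −1.09, power 14%.
- Non-events, n = 61: (0.075 − 1.96×0.0668)/0.0665 = −0.84, power 20%.
- At risk only, n = 30 (half of 61, rounded down): (0.15 − 1.96×0.1209)/0.1194 = −0.73, power 23%.

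**Range over f, with pC = 40% and pT = 20%** (at-risk difference 20 points, relative risk 0.50)

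| f | Difference, all patients | RR, as events | RR, as non-events | Power, as events | Power, as non-events | Power, at risk only (n per group) |
|---|---|---|---|---|---|---|
| 0.2 | 16 points | 0.69 | 0.50 | 43% | 54% | 58% (48.8) |
| 0.4 | 12 points | 0.81 | 0.50 | 27% | 41% | 46% (36.6) |
| 0.6 | 8 points | 0.90 | 0.50 | 16% | 27% | 33% (24.4) |

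These powers leave out the multiplicity step in the plan, in which the χ² test is "followed by the Bonferroni method will be used to evaluate the comparison of categorical variables". With all six pairs at 0.05/6, the f = 0.4 row falls to 10%, 18% and 22%. The order is the same.

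**Chance imbalance.** At f = 0.5, the standard error of the difference in baseline intubation between two groups is √(2×0.5×0.5/61) = 0.0905, about 9 points. Counted as events, an imbalance δ shifts the rate by δ(1−p). For δ of 9 points that is 0.0905×0.60 = 5.4 points at p = 40% and 0.0905×0.75 = 6.8 points at p = 25%, against a diluted effect of 7.5. Counted as non-events, the shift is only δp: 3.6 and 2.3 points. The power figures above already include this noise.

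**Hyperglycaemia.** If patients on insulin at entry count as events, the second pair of formulas applies, with f replaced by the share on insulin. That share is not given, and no size is claimed.

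**The case against.** Several points on the other side carry weight.

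- **The share is unknown.** With three routes into the trial and no stated mix, a reader might infer that many patients are intubated at entry and that the rate mostly reflects baseline status. The article supports neither. The second inference also fails outright if baseline cases count as non-events, because the rate then contains only new intubations.
- **The milder reading is arguably the more natural one.** Needing intubation within 28 days of randomisation suggests intubation after that point. The relative risk is then preserved, and the fix gains about 3 points of power in the first example and 4 to 6 in the table. The outcome is poorly powered either way.
- **Re-intubation is possible.** It would be too strong to say that patients ventilated at entry cannot have the event at all. They cannot have a first new intubation. How a re-intubation counts is also left open.
- **An all-randomised denominator respects intention to treat,** and a coding rule might stand in a fuller document. This stands only in part. The article does state a definition, and that definition sits badly with its own entry criteria. Restricting by a status fixed before treatment keeps the randomised comparison.
- **Hyperglycaemia.** A reader might conclude that a dose-related harm will be hidden. The article does not show that. Controlled diabetes need not mean insulin, and all adverse events are collected. Attenuation is possible; its extent is unknown.
- **Other outcomes.** It is tempting to restrict temperature recovery and vasopressor duration in the same way. No comparable defect is shown for them, and limiting vasopressor duration to patients on vasopressors at entry would drop shock that begins after randomisation.

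Ventilator-free days and ventilation duration also measure ventilation burden in all patients, which limits the consequence.

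**Conclusion.** The point holds as an inexpensive improvement to a secondary outcome. As defined, the intubation rate mixes patients at risk with any who are already intubated, and it does not say how the latter count. For any f above zero, and without re-intubation, the risk difference is (1−f) times the at-risk difference under either coding. The relative risk moves toward 1 only if baseline cases count as events. In the scenarios tested, the at-risk analysis had more power than either all-patient coding, by a small margin over non-event coding and a larger one over event coding. All sizes rest on assumed values of f and of the intubation rates. For hyperglycaemia, the supported statement is that counting patients already on insulin may attenuate a difference between doses.

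**What to change.** Define the outcome as new endotracheal intubation after randomisation, within 28 days, among patients not intubated at randomisation. Report that denominator by group, and report death without intubation alongside, since a patient who dies untubed can no longer have the event. State how re-intubation is handled in patients ventilated at entry.

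Define hyperglycaemia as a new or increased insulin requirement after the first dose, where baseline insulin use is recorded.

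For intubation the cost is wording and a smaller denominator; ventilation status at entry is already known from eligibility. For hyperglycaemia the cost depends on whether baseline insulin use is captured, which the article does not show. Recruitment began in April 2021, so patients already enrolled might need a look back at their records.

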### Design

Patients with diagnosed SCAP are randomized to the following four groups at a 1:1:1:1 ratio:Group 1 (control group): standard ICU patient care+100ml of normal saline once a day for 5 days. Standard ICU patient care involves ventilatory, hemodynamic, antimicrobial, nutritional, and other supports according to the guidelines for the diagnosis and treatment of community-acquired pneumonia in Chinese adults (2016 Edition). At present, there are no relevant guidelines to recommend methylprednisolone as a therapeutic drug for SCAP, which indicates that a consensus has not been reached and disputes still exist. Thus the placebo control group is still needed.Group 2: standard ICU patient care+40mg of methylprednisolone (dissolved in normal saline with a final volume of 100ml) once a day for 5 days.Group 3: standard ICU patient care+80mg of methylprednisolone (dissolved in normal saline with a final volume of 100ml) once a day for 5 days.Group 4: standard ICU patient care+120mg of methylprednisolone (dissolved in normal saline with a final volume of 100ml) once a day for 5 days.

Researchers will explain the research procedures in detail to the subject or agent to obtain the informed consent and will evaluate intervention adherence during each visit. If a scheduled visit is delayed or canceled, the research team will contact the subject immediately. No concomitant care or intervention is prohibited during the study. The trial is planned to be followed up for 28 days after randomization. The schedule of enrolment, interventions, and assessments is shown in Fig. 1.

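### The endotracheal intubation rate is not restricted to patients at risk, although patients already on invasive ventilation can be randomised

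*Protocol article*

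**What the plan says.** Protocol article, Participants: SCAP requires the CAP criteria plus "one of the following major criteria or more than three minor criteria, he/she can be diagnosed as SCAP". The major criteria are given as "Major criteria:Invasive mechanical ventilationSeptic shock with the need for vasopressors". One of them suffices, so invasive ventilation on its own completes the SCAP definition. Nothing in the exclusion criteria removes such patients.

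Secondary outcomes: "Endotracheal intubation rate (the proportion of patients requiring endotracheal intubation within 28 days of randomization". The definition has a time window. It does not say that the intubation must be new, and it does not limit the outcome to patients not yet intubated.

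Statistical analysis: "Data for the primary and secondary outcome will be analyzed on intention-to-treat analysis". For categorical outcomes, a χ² "test followed by the Bonferroni method will be used to evaluate the comparison of categorical variables". The only provision that might bear on ventilation status at entry is "Subgroup analysis will be used when appropriate", which names no subgroup.

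The article gives no expected share of patients intubated at entry and no expected intubation rate.

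**The concern.** A patient who is intubated before the first infusion cannot have that intubation prevented by any of the study doses. Such a patient enters the outcome in one of two ways. If existing intubation counts, the patient is an event in whichever arm he or she is allocated to. If only new intubations count, the patient is almost always a non-event (re-intubation after extubation is the exception) but stays in the denominator. The definition does not choose between the two, and the same data would give two different rates.

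Under either reading these patients add numbers but next to no information on the dose effect, so the difference between arms is diluted. At stake is the interpretation of one secondary outcome: a null result could reflect the mix of patients at entry rather than the absence of an effect.

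**Working it through.** **The plan's own figures.** There is no sample size or rate for this outcome to reproduce. The arm size comes from the primary outcome calculation: "220 participants will be required (55 in each group"), inflated for 90% follow-up. 220 / 0.9 = 244.4, stated as 244, and 244 / 4 = 61 per arm.

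**Inputs.**
- n = 61 per arm (Sample size section).
- α = 0.05 (Statistical analysis section), taken as two-sided, one pair of arms. Four arms give six pairs, so the Bonferroni level is 0.05/6.
- m, the share intubated at entry: not in the documents, so varied.
- a and b, the 28-day intubation risks in two arms among patients not yet intubated: not in the documents. Main assumption 40% vs 20%; range 30% vs 15% and 50% vs 25%.

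**Observed rates.**
- Reading A (existing intubation counts as an event): m + (1 − m)a vs m + (1 − m)b.
- Reading B (only new intubations count, all randomised patients in the denominator): (1 − m)a vs (1 − m)b.
- At-risk analysis: a vs b with n = 61(1 − m).

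In A and B alike the absolute difference is (1 − m)(a − b). The risk ratio moves towards 1 in A and stays at b/a in B.

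**Power formula.** Φ{[|p₁ − p₂|√n − z√(2p̄(1 − p̄))] / √(p₁(1 − p₁) + p₂(1 − p₂))}, with p̄ the mean of p₁ and p₂, and z = 1.96 at two-sided 0.05.

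Worked example, m = 0.5, 40% vs 20%:
- A: 0.70 vs 0.60, n = 61: (0.781 − 1.322)/0.671 = −0.81, power 0.21.
- B: 0.20 vs 0.10, n = 61: (0.781 − 0.990)/0.500 = −0.42, power 0.34.
- At risk: 0.40 vs 0.20, n = 30.5: (1.105 − 1.270)/0.632 = −0.26, power 0.40.

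**Results, 40% vs 20%, one pair, two-sided 0.05.**

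| m | Rates in A | Risk ratio in A | Power A | Power B | Power at risk |
|---|---|---|---|---|---|
| 0 | 40% / 20% | 0.50 | 68% | 68% | 68% |
| 0.2 | 52% / 36% | 0.69 | 43% | 54% | 58% |
| 0.3 | 58% / 44% | 0.76 | 34% | 48% | 52% |
| 0.5 | 70% / 60% | 0.86 | 21% | 34% | 40% |
| 0.8 | 88% / 84% | 0.95 | 9% | 15% | 18% |

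At 0.05/6 with m = 0.5, power is 7% (A), 14% (B) and 17% (at risk).

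**Range over the assumed risks, two-sided 0.05 (A / B / at risk).**
- 30% vs 15%: 28% / 41% / 43% at m = 0.2; 13% / 26% / 29% at m = 0.5.
- 50% vs 25%: 60% / 68% / 73% at m = 0.2; 32% / 42% / 52% at m = 0.5.

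In every scenario with m above zero the at-risk analysis has the most power, despite its smaller denominator.

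**Patients needed for 80% power**, 40% vs 20%, m = 0.5: 356 per arm under A, against 164 randomised per arm if only those at risk are analysed.

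**The case against.** The strongest reply is that reading B is the more natural one. The same section uses the 28-day window for death, bleeding and nosocomial infection, all of which occur after randomisation, and intubation can be read in the same way. Under B the risk ratio is preserved and, at 40% vs 20%, restricting to those at risk gains only about 2 to 6 percentage points of power (10 points in the 50% vs 25% case at m = 0.5). This stands, and it limits the size of the problem. It does not settle the definition, because the text does not say that only new intubations count.

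A reader might infer more than the documents support:
- *That the dose effect is swamped, or that the outcome mainly records who arrived on a ventilator.* Patients can also enter through septic shock or minor criteria, and m is not given. The loss is severe only under reading A with a large m.
- *That chance imbalance in entry intubation creates false dose effects.* A 15-point imbalance would shift the outcome by 15 × 0.60 = 9 points under A, or by 15 × 0.40 = 6 points the other way under B, at a 40% risk. But chance imbalance is already covered by the test's error rate: simulated type I error under A with m = 0.5 was 5.0%. With simple randomisation and m = 0.5, the largest gap over the six pairs reaches 15 points in 31% of trials; for one given pair it does so in about 8.5%.
- *That this is one of few outcomes that matter to patients.* The list also has mortality at 28 and 60 days, ventilator-free days, ventilation duration, vasopressor duration and hospital stay.
- *That deaths without intubation must be built into the outcome.* Such a patient does score as not intubated, but mortality is reported separately at two time points, so a composite is a choice and not a correction.

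Finally, this is a condensed article, and a fuller protocol or SAP might set the denominator. That would excuse silence. Here, however, the article states a definition and an analysis principle which, taken with its entry criteria, do not fit together. The open-ended subgroup sentence does not change the definition.

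**Conclusion.** The point holds in a limited form. By the protocol's own entry criteria, patients already intubated can be randomised. The intubation rate is defined without an at-risk restriction and analysed by intention to treat, and how these patients count is left open. The absolute difference between arms shrinks by the factor (1 − m) under both readings.

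The size rests on assumptions, because neither m nor the intubation risk is in the documents. With 40% vs 20% and 61 per arm, the loss of power against an at-risk analysis is 15 points (A) or 4 points (B) at m = 0.2, and 19 or 6 points at m = 0.5. Attenuation of the risk ratio, from 0.50 to 0.69 and 0.86, occurs only if existing intubations count as events. The outcome is weakly powered even with nobody intubated at entry (68%). It is a secondary outcome, and the primary conclusion does not depend on it.

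**What to change.** Define the outcome as new endotracheal intubation within 28 days of randomisation among patients not intubated at randomisation. Analyse these patients in the arm to which they were randomised. The set is fixed by a baseline characteristic, so the comparison remains randomised and consistent with intention to treat. Report the number already intubated per arm as a baseline characteristic.

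The cost is a sentence or two in the definition and a smaller denominator for this one outcome. No new data should be needed, because invasive ventilation is assessed for eligibility. A composite of intubation or death without intubation could be added as a sensitivity analysis but is not required; the power figures above are for intubation alone and do not evaluate it.
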